#### **7.8 Dispensing of Investigational Product**

The dispensing pharmacist will dispense a quantity of the investigational products sufficient for dose administration well in advance as per the randomization schedule in presence of Quality Assurance (QA) and the remaining Investigational Products will be kept in their original containers. Individual subject supplies for each visit in HDPE bottles will be packed and labelled according to local regulations. For dispensing at Veeda, each subject bottle will contain sixteen tablets (14 for study drug medication once daily and 2 for extra) per visit while for dispensing at AMC, each subject will be provided bottles with 30 tablets/bottle (including 2 reserve tablets). For last dosing on day 28, subject will visit the site on day 27 and subject will be asked to take a tablet (last dose) under supervision.

## **8. METHODS**

### **8.1 Study parameters/endpoints**

#### **8.1.1 *Main study parameter/endpoint***

To determine safety and efficacy for TRC150094 in increasing hepatic and peripheral insulin sensitivity

#### **8.1.2 *Secondary study parameters/endpoints***

To determine the effect of TRC150094 on hepatic fat and multiple metabolic parameters

### **8.2 Randomisation and treatment allocation**

#### **8.2.1 *Preparation of randomisation code***

The randomisation code and sealed individual code-break envelopes will be prepared by the clinical research unit at each site. One set of the individual code-break envelopes will be prepared and provided to the investigator. Each research unit will prepare three randomization lists for statistician, pharmacist and sponsor respectively. The randomisation code will specify whether the subject receives TRC150094 or placebo dosing over the course of the study period. The randomisation code will be in consecutive sequence at the two study centres; hence at one unit it will be 001-020 and other unit it will be 021-040. The randomization list provided to the sponsor nominated individual (who is not directly associated with the study) will be sealed. The seal will be ensured at the end of study. All randomisation information will be secured and kept in a locked storage area, accessible only by authorised personnel. Only subjects who meet all of the inclusion criteria and none of the exclusion criteria are eligible for randomisation. Randomisation will take place on Day 0, the day before dosing. Subjects will be randomized to receive either placebo or TRC 150094 in 1:1 ratio. Each subject will be given a subject number (equivalent to the randomisation number). This number will be a consecutive number from 001 onwards. It will be assigned in the order of the inclusion of subjects at the first dosing.

#### **8.2.2 *Breaking the randomisation code***

The investigator will have access to one set of sealed code-break envelopes. In the event of an emergency, e.g. a serious adverse event (SAE), the investigator may open the subject's envelope to determine the study drug administered to the subject. If

---

possible, the sponsor should be notified before the blind is broken; otherwise, the sponsor will be notified as soon as possible. In addition the IEC (Independent Ethics Committee) will also be notified if the code is broken during the study. The date, time and reason, and the name of the person who opened the envelope, will be recorded in the subject's CRF and on the individual envelope. If the blind is broken, the subject must be withdrawn from the study and replaced.

### **8.3 Blinding**

This will be a double-blind design. The subjects and investigator (and other personnel involved in the study) will be unaware of the study drugs administered to individual subjects.

Personnel in the biometrics department at Academic Medical Centre and Veeda Clinical Research will be blind during the study, except for a nominated individual(s) responsible for preparing the randomisation code and code-break envelopes. The sponsor will remain blind during the study. The placebo tablets will be identical in appearance and taste to the TRC150094 tablets administered at the corresponding dose level, and the same number will be administered. Pharmacy personnel at the study centre who prepare and check the individual unit doses from the bulk packaging will be the only staff at the study centre that is not blind to the study drug. At regular monitoring visits, a study monitor will check the blind is maintained during dosing and during the study, and that all code-break envelopes remain intact. The monitor will remain blind during the study, and steps must be taken during monitoring such that treatment allocation is not revealed.

### **8.4 Study Procedures**

This section describes the Hyperinsulinemic Euglycemic Clamp and Magnetic resonance spectroscopy (MRS) procedures

#### **8.4.1 *Hyperinsulinemic Euglycemic Clamp***

The clamp procedure will be performed twice on each subject (on Day 0 and Day 28) after an overnight fast. A deviation up to +2 days is acceptable only in those cases that missed doses within the limits given above and has continued planned medication up to day of post-dose investigations. Participants will be admitted to the trial unit and studied in the supine position. During the procedure, the participants are only allowed to drink water. Following a 13 hr fast, a catheter will be inserted in the vein of each

---

arm. One catheter is used for sampling of arterialised blood using a heated hand box (60°C). The other catheter is used for infusion of [6,6-2H2]-glucose en and [1,1,2,3,3-2H2]-glycerol, glucose 20% and insulin. At t= -2hr, after drawing a blood sample for background enrichment of plasma glucose, a continuous infusion of [6,6-2H2]-glucose (>99% enriched, Cambridge Isotopes, Massachusetts, USA) is started at a rate of 0.11 µmol/kg per min after a priming dose equivalent to 100 min of infusion. After 1 hr, a continuous infusion of [1,1,2,3,3-2H2]-glycerol (>99% enriched, Cambridge Isotopes, Massachusetts, USA) is started at a rate of 0.11 µmol/kg per min after a priming dose of 1.6 µmol/kg/min. The first 2 infusion hrs are required for equilibration. After 115, 120 and 125 min blood samples are drawn for determination of glucose and glycerol enrichment to calculate basal endogenous glucose production and lipolysis, glucoregulatory hormones and FFA. Subsequently, the hyperinsulinemic clamp will start with a continuous infusion of insulin (Actrapid 100U/ml, Novo Nordisk ) for 2hr at a rate of 20mU/m^2 body surface area per min. Plasma glucose is measured every 10 min (Biosen C-line plus glucose analyzer; EKF Diagnostics, Barleben/Magdeburg, Germany at AMC, Netherlands; and YSI analyzer at Veeda Clinical Research India) and glucose 20% is infused at a variable rate to maintain plasma glucose at 5.0 mmol/l or 90 mg/dl. [6,6-2H2]-glucose is added to the 20% glucose solution to achieve glucose enrichments of 1% to minimize changes in isotopic enrichment due to changes in the infusion rate of exogenous glucose, and thus to allow for accurate quantification of endogenous glucose production and uptake. During the last 20 min of the hyperinsulinemic clamp, blood samples are drawn at 5 min intervals for determination of glucose and glycerol enrichment, glucoregulatory hormones and FFA. At t= 2.15hr, the infusion of insulin is increased to a rate of 60mU/m^2 body surface area per min. Plasma glucose is measured again every 10 min and enriched glucose 20% is infused at a variable rate to maintain plasma glucose at 5.0 mmol/l or 90 mg/dl. During the last 20 min of this insulin infusion step, blood samples are drawn at 5 min intervals for determination of glucose and glycerol enrichment, glucoregulatory hormones and FFA. Thereafter insulin infusion will be discontinued and participants will be offered a carbohydrate rich meal. The glucose infusion rate will be doubled. Plasma glucose levels will be measured every 10 minutes for the first hour. Thereafter blood glucose measurement will be done at 20 minute intervals or more frequently (at the discretion of the

---

---

investigator). Every time plasma glucose levels are > 7 mmol/l the glucose infusion rate will be halved until less than 5 ml/hr. Four weeks later, the second clamp will be performed with the same methodology.

Name and description of investigational product(s)

- [6,6-2H2] labelled glucose, Cambridge isotopes, Cambridge, Massachusetts, USA
- [1,1,2,3,3-2H2] labelled glycerol, Cambridge isotopes, Cambridge, Massachusetts, USA
- Actrapid, Novo Nordisk
- Glucose 20%

[6,6-2H2] labelled glucose and [1,1,2,3,3-2H2] labelled glycerol will be involved at the pharmacy at the study centre and will be prepared by the investigators.

Endogenous glucose production (EGP) and peripheral glucose uptake (Rd) are calculated using the modified form of the Steele equations. Lipolysis (glycerol turnover) will be calculated by using formulas for steady state kinetics adapted for stable isotopes.

#### **8.4.2 Quantification of Hepatic Fat.**

Hepatic will be measured by H MRS on Day 0 and Day 28. A deviation ± 2 days is acceptable. The analysis and interpretation of MRS data will be done by core lab of Academic Medical Centre at Amsterdam, The Netherlands. During the measurements, the subjects will lie down inside the magnet of a clinical magnetic resonance spectrometer with a body array surface coil positioned around the abdomen. For the quantification of liver fat, localized single voxel proton MR spectra from the liver will be obtained without water suppression using long repetition time and short echo time to minimize relaxation effects on signal intensity. The MRS measurement will be carried out without breath holding. Spectral signal intensities of water and methylene groups originating from the lipids will be fitted to determine the percentage of intracellular triglycerides of the hepatocytes.

---

#### **8.4.3 Silent Information Regulator T (SIRT) expression study:**

Modulation of SIRT expression will be monitored for Indian cohorts only. For this purpose, 10ml of heparinised blood will be collected. Peripheral blood mononuclear cells (PBMNCs) will be isolated using HISTOPAQUE within 2 hrs of blood collection. Isolated PBMNCs will be stored at -80°C. Total RNA will be isolated from PBMNCs and SIRT gene expression will be monitored employing specific probes by real-time PCR. Modulation of SIRT expression will be monitored for each volunteer at Day 0, Day 14 and Day 28 of the study. A deviation of  $\pm 1$  day is acceptable. Analysis of samples for SIRT expression will be performed at Cell and Molecular Biology Lab, Torrent, India.

Total 30 ml heparinised blood per volunteer will be required.

#### **8.4.4 Measurement of Sagittal Abdominal diameter**

Sagittal abdominal diameter will be measured in the supine position with bent knees on a firm examination table. The measurement will be done to the nearest 0.1 cm after a normal expiration and without clothes in the measurement area. Sagittal abdominal diameter will be measured at the level of iliac crest (L4–5) using a sliding-beam caliper, as the distance between the examination table up to the horizontal level, allowing the caliper arm to touch the abdomen slightly but without compression.

### **8.5 Study Visits**

#### ***Screening***

Subjects will attend the CRU for a screening visit up to 28 days before their Baseline investigation (Day 0). Prior to attending for a screening visit, subjects will be asked to comply with certain exercise and dietary restrictions, as specified in Section 6.7. Informed consent must be obtained at this visit before any study procedures are performed. Further details regarding informed consent are provided in Section 11.2. A screening log will be kept to record subjects who sign the informed consent form and who are screened. For those subjects who are screen failures, a reason will be documented. The following assessments/information will be performed/ recorded

- date of birth and age
- race

- 
- height and body weight (measured while wearing indoor clothing and no shoes)
  - waist circumference
  - body mass index (BMI), calculated as weight (kg)/height (m)
  - smoking status / intake of tobacco in any other form (including current and historical use of tobacco, and ability to stop smoking / tobacco intake in any other form, for study periods)
  - medical history (any significant conditions or diseases that stopped at or prior to screening)
  - pre-existing (concurrent) conditions (those present at the screening visit)
  - prior and ongoing medication (medications taken up to 4 weeks prior to first dose)
  - full physical examination
  - vital signs (supine and standing) and body temperature
  - 12-lead ECG
  - chest X-ray (to exclude active tuberculosis, in India only)
  - clinical laboratory tests (blood sample for haematology and biochemistry tests; and urine sample for urinalysis)
  - lipid Parameters
  - viral serology (hepatitis B surface antigen [HBsAg], hepatitis C antibody, human immunodeficiency virus [HIV I and HIV II])
  - alcohol breath test
  - urinary drugs of abuse screen (amphetamines, barbiturates, benzodiazepines, cannabinoids, cocaine, opiates and methadone).

Those subjects who are eligible for the study, based on the inclusion and exclusion criteria, will be invited to take part in the study. Lifestyle instructions as mentioned in Section 6.7 will be given.

*Day 0*

---

Those subjects who meet all inclusion and none of the exclusion criteria and who have given their informed consent will be asked to come to the CRU for baseline investigations on Day 0. On Day 0 subjects will visit the study centre early in the morning after a 13 hr fast. If it is not possible for a subject to arrive at the study centre this early in the morning, the subject is offered to stay overnight. The subjects may be asked to visit the CRU on Day-1 for some baseline investigations (at the discretion of Principal Investigator). Randomisation will take place on Day 0.

At Day 0 the following assessments will be performed

- physical examination
- vital signs
- 12-lead ECG
- height and body weight
- waist circumference
- Sagittal abdominal diameter
- clinical laboratory tests (Haematology, Biochemistry, urine analysis)
- Blood Sample for SIRT expression (see Appendix B)
- lipid Parameters
- hepatic MRS – See Section 8.4.2 (a deviation of  $\pm 2$  days is acceptable for MRS)
- compliance to drug and life style instructions
- AEs and change in concomitant medications will be reported
- hyperinsulinemic euglycemic clamp, the clamp procedure is described in Section 8.4.1

#### *Treatment Period Day 1-28*

Each subject will receive once daily dosing in the morning for Day 1-28 under fasting conditions (see Section 7.5)

#### *Day 14*

---

On Day 14, subjects will visit the CRU after an overnight fast. A deviation  $\pm 1$  day is acceptable. The following assessments will be performed:

- vital signs
- height and body weight
- waist circumference
- Safety clinical laboratory tests (Haematology, Biochemistry, urine analysis)
- Blood Sample for SIRT expression (see Appendix B)
- lipid Parameters
- 12-lead ECG
- AE check and change in concomitant medications will be recorded
- compliance to drug and Life style instructions

#### Day 28

On Day 28 subjects will visit the study centre early in the morning after a 13 hr fast. A deviation up to +2 days is acceptable only in those cases that missed doses within the limits given above and has continued planned medication up to day of post-dose investigations. If it is not possible for a subject to arrive at the study centre this early in the morning, the subject is offered to stay overnight. The subjects may be asked to visit the CRU on Day 27 for some end-of-treatment investigations (at the discretion of Principal Investigator).

At Day 28 the following assessments will be performed.

- physical examination
- vital signs
- 12-lead ECG
- height and body weight
- waist circumference
- Sagittal abdominal diameter
- clinical laboratory tests (Haematology, Biochemistry, urine analysis)
- Blood Sample for SIRT expression (see Appendix B)
- lipid Parameters

- 
- hepatic MRS– See Section 8.4.2 (a deviation of  $\pm 2$  days is acceptable for MRS)
  - AEs and change in concomitant medications will be reported
  - hyperinsulinemic euglycemic clamp, the clamp procedure is described in Section 8.4.1
  - Compliance to drug and Life style instructions
  - Discontinuation of study drug

At follow up visit (Day 35), subjects will visit the study centre after an overnight fast.

*Follow up visit*

Follow-up visit is planned at Day 35. A deviation of + 3 days is acceptable.

At Day 35 the following assessments will be performed:

- Physical examination
- Vital signs
- Height and body weight
- Waist circumference
- Safety clinical laboratory tests (Haematology, Biochemistry, urinalysis)
- Lipid Parameters
- 12-lead ECG
- AEs and change in concomitant medications will be reported
- Restart of metformin treatment (if applicable)

**8.5.1 . Clinical laboratory tests**

A blood sample will be taken for measurement of haematology and biochemistry parameters, and a urine sample will be taken for urinalysis at the following time points:

- screening visit
- Day 0
- Day 14
- Day 28

- 
- Day 35

The Laboratory parameters and time-points are specified in (Appendix A) and (Appendix B).

#### **8.5.2 Vital signs**

Body temperature and supine vital signs (blood pressure and heart rate) will be measured on the non-dominant arm after 5 minutes of supine rest on the Day of screening visit, Day 0, Day 14±1 and Day 28 (t = -2hr) and at follow up (See Appendix B). Standing vital signs (blood pressure and heart rate) will also be measured at the screening visit. Standing vital signs will be measured after the supine values have been recorded and after the subject has been standing for 2 minutes. These measurements will be used to calculate the postural drop in blood pressure. Vital sign measurements will be performed within ±10 minutes of the scheduled time points

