metabolic rate and lowering atherogenic serum lipoproteins are clinically interesting metabolic responses since these could hypothetically be of use to treat obesity and its related co-morbidities. However previous attempts to mimic the effects of THs using thyroid hormone metabolites and analogues have been complicated by the induction of thyrotoxic adverse effects in other organ systems such as the heart and skeleton. Consequently, the development of a TH agonist or analogue that retains anti obesity efficacy while being devoid of thyrotoxic effects, would represent a potentially valuable therapeutic approach for obesity related co-morbidity. T2 (3,5-diiodothyronine) is a metabolically active iodothyronine with the capacity to stimulate oxidation of fatty acids in metabolically active tissues (heart, skeletal muscle, liver and Brown adipose tissue) at relatively low concentrations. T2 has lesser affinity towards the thyroid receptor compared to T3 and its metabolic effects are rapid.

TRC150094 is a novel thyromimetic analogous to 3,5-diiodothyronine (T2) being developed by Torrent for the treatment of Cardiometabolic risk associated with non-traditional risk factors.

TRC150094 is a thyromimetic analogous to T2 that aims at increasing the energy expenditure and thus regaining the balance.

In various preclinical studies conducted in multiple animal models of visceral adiposity, insulin resistance and metabolic syndrome, it was found that TRC150094 increases energy expenditure through increase in mitochondrial metabolic activity and attenuates visceral adiposity, atherogenic dyslipidemia, blood pressure and improved insulin sensitivity.

If these effects are replicated in clinical setting, this profile will prove invaluable in the treatment of Cardiometabolic risk associated with visceral adiposity.

Clinically, the continuous administration of TRC150094 administration leading to sustained increase in Energy Expenditure is expected to result in:

- Decrease in adiposity leading to a more desirable body mass composition,
- Decrease in hepatic fat thus improvement in NAFLD,

- 
- Improvement in insulin sensitivity thus improvement in glucose homeostasis,
  - Improvement in insulin sensitivity, dependent renal-hormonal axis (RAAS and SNS), endothelial function and thus, improvement in Blood Pressure profile,
  - Improvement in lipid profile.

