### **6.2 Inclusion Criteria**

Subjects will be considered eligible for entry in the study if they meet all of the following criteria.

1. Adult male
2. Age range 30–65 years at screening
3. Caucasian or Indian Ethnicity
4. Waist circumference  $\geq 102$  cm for Caucasians and  $\geq 90$  cm for Indians at screening.
5. Fasting Serum Insulin  $\geq 10$  mU/ml at screening
6. Blood Pressure  $\geq 130/85$  mmHg at screening (or patients taking medication for hypertension)
7. Stable weight during 3 months prior to the study (assessed through medical history of the patient)
8. Drug naïve diabetic patients\* or patients with impaired fasting glucose i.e  $> 100$  mg/dl or  $5.5$  mmol/l and  $< 200$  mg/dl or  $11.0$  mmol/l. Diabetic patients who were taking metformin and have undergone washout for at least 4 weeks before Day 0 and are currently on life style modification as a treatment for diabetes will also be allowed in the study
9. Willingness to give written informed consent (prior to any study-related procedures being performed) and ability to adhere to the study restrictions and assessments schedule.

---

**\* Diabetic patient is defined as a patient with a documented history of type II DM or a documented history of a fasting glucose > 200 mg/dl or 11.0 mmol/l or 2x fasting glucose > 126 mg/dl or 6.9 mmol/l (2x = recorded twice)**

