#### **Single Dose Studies:**

The Single Dose Studies included:

**PART A:** Single ascending dose in non-elderly and elderly overweight/obese male and female subjects to evaluate safety, tolerability and pharmacokinetics of TRC150094.

**PART B:** To evaluate effect of food on pharmacokinetics of TRC150094 in young healthy male and female subjects and to assess the safety and tolerability of single oral doses of TRC150094 administered in fasted and fed states.

A total of 40 subjects were randomized in Part A. Out of 40 subjects, 24 were non-elderly overweight/obese subjects aged 18-65 years and 16 were elderly aged above 65 years. 24 subjects were divided in 3 cohorts (Cohort 1: 5 and 100mg; Cohort 2: 25 and 200 mg; Cohort 3: 50 and 400 mg) each having 8 subjects and 16 elderly subjects were assigned to fourth cohort (50 and 150 mg). Out of 24 non-elderly subjects, 18 were administered TRC150094 and 6 were administered placebo. Among elderly subjects, 12 were administered TRC150094 and 4 were administered placebo. Each subject received two dose levels with a washout period of 7 days in between the two study periods. In Part B of the study 6 healthy subjects aged 18-65 years were randomized to receive the active dose of 100 mg in fasting and fed conditions, with a washout period of atleast 7 days between the two study periods.

The main findings of these studies are as follows:

Safety and tolerability- The ascending doses of TRC150094 ranging from 5 mg to 400 mg, evaluated in the study were found to be safe and well tolerated in both elderly, as

---

well as non-elderly overweight/obese subjects. There were no SAEs or withdrawals due to AE in the study. All the adverse events were mild to moderate in nature. In non-elderly cohort, headache was the most common AE experienced by 3 (8.3%) subjects followed by decreased appetite, pain in extremity and dizziness postural, each experienced by 2 (5.6%) subjects in the TRC150094 group. Headache was the most common AE experienced by 2 (8.3%) subjects in the elderly cohort, also, followed by back pain experienced by 1 (4.2%) subject receiving TRC150094. No AE was reported in the placebo group in elderly cohort.

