### **7.3 Dose Administration**

Dosing will start on Day 1. It is planned that each subject will receive once daily dosing (tentatively 50 mg) in the morning for Day 1-28 under fasting conditions with a glass of water. Uniformity in timing of intake of medication will be advised which should be preferably within  $\pm 1$  hr of the time of intake of study medication on Day 1. The dosing will not be under direct supervision (except Day 28 dosing); the subjects are required to maintain a diary where they will make entry for the daily dosing. The subjects will be advised not to take any food for at least 1 hr prior to dosing and for 1 hr post-dose. For outpatient days (i.e. on days 1 to 28) drug supply in appropriately labelled bottles will be provided to the subjects. The subjects will be instructed to carefully document the time of drug consumed and time of meals and exercise, in the diary cards provided to them. Subjects will be asked to bring the remaining drugs with the diary cards during intermediary visit to the clinic. The study pharmacist or technician will carry out drug reconciliation and ensure compliance of the subject is satisfactory. Appropriate documentation of the subject specific dispensing process must be maintained. The batch number of each study drug administered to each subject will be recorded in Pharmacy documents.

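### Standing blood pressure is taken only at screening, so a postural fall on treatment can be neither measured nor compared with placebo

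*Protocol*

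**What the plan says.** Section 8.5.2 schedules body temperature and supine blood pressure and heart rate after "supine rest on the Day of screening visit, Day 0, Day 14±1 and Day 28 (t = -2hr) and at follow up". The upright reading is tied to one visit: "Standing vital signs (blood pressure and heart rate) will also be measured at the screening visit". It follows the supine reading, after 2 minutes on the feet, and its purpose is given: "These measurements will be used to calculate the postural drop in blood pressure".

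The visit lists in section 8.5 agree. The screening list has "vital signs (supine and standing) and body temperature". The lists for Day 0, Day 14, Day 28 and Day 35 say only vital signs. Appendix B has a single undivided vital-signs row and adds no standing reading. Section 7.3 states: "Dosing will start on Day 1".

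Four other places bear on the point:
- Section 4.1 makes safety part of the primary objective.
- Section 7.2.3 (single-dose studies, non-elderly cohort) names headache as the most common event, "followed by decreased appetite, pain in extremity and dizziness postural, each experienced by 2 (5.6%) subjects in the TRC150094 group".
- Section 6.2, criterion 6, requires raised blood pressure at screening "or patients taking medication for hypertension". Section 6.3, criterion 3, allows stable ACE inhibitors or ARBs.
- Section 3 lists "improvement in Blood Pressure profile" among the expected effects of continued dosing.

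**The concern.** The protocol defines a postural measurement and says what it is for, but schedules it only where the study drug cannot have affected it. After screening, the blood pressure and heart rate summaries planned in section 10.4 rest on supine values alone. No analysis plan can recover standing readings that were never taken.

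A placebo-controlled look at postural blood pressure is at stake, in men who may be on antihypertensives and are taking a drug expected to lower blood pressure. If a subject reports dizziness on treatment, no scheduled reading shows whether pressure fell on standing. A fall without symptoms leaves no trace. The independent physician's review in section 9.1.1 would not fill the gap, because the parameters named there are laboratory tests, urine analysis and ECG.

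**Working it through.** **1. Where a postural drop can be calculated.** It needs a supine and a standing reading at the same visit (sections 8.5 and 8.5.2, Appendix B).

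| Visit | Relation to dosing | Supine | Standing | Drop available |
|---|---|---|---|---|
| Screening | before | yes | yes | yes |
| Day 0 | before | yes | no | no |
| Day 14 | on treatment | yes | no | no |
| Day 28 | end of treatment | yes | no | no |
| Day 35 | after | yes | no | no |

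That is 1 of 5 visits overall and 0 of 2 on treatment. The one available drop precedes randomisation, so it supports no comparison of drug with placebo.

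**2. The protocol's own figure for postural dizziness.** Inputs from section 7.2.3: 18 non-elderly subjects received TRC150094, each at two dose levels, and 2 had postural dizziness.
- Exposures: 18 × 2 = 36.
- 2/36 = 5.6%, the printed figure. Headache reproduces the same way: 3/36 = 8.3%.
- The elderly figures confirm that the denominator is exposures: 12 × 2 = 24, with 2/24 = 8.3% and 1/24 = 4.2%, as printed.
- Per subject: 2/18 = 11.1%. The exact (Clopper-Pearson) 95% interval is 1.4% to 34.7%.

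The interval is wide because there are only two cases. They are pooled over single doses from 5 to 400 mg. The dose at onset and the rate in the 6 non-elderly placebo subjects are not given.

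**3. What added readings could show.** Section 6.1 plans 10 active and 10 placebo subjects per site, so 20 per arm. The protocol gives no SD for the change in postural drop; assume 8 to 15 mmHg. The half-width of the between-arm 95% interval is 1.96 × SD × √(2/20):
- SD 8: 1.96 × 8 × 0.316 = 5.0 mmHg.
- SD 15: 1.96 × 15 × 0.316 = 9.3 mmHg.

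That is precise enough to show a large mean effect, but not a small one.

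**4. Which visits matter.** Section 7.2.3 gives a half-life of 15 to 18 h. Seven days after Day 28 is 168 h, and 168/18 = 9.3 to 168/15 = 11.2 half-lives. Day 35 is therefore essentially off drug. Day 0 supplies the baseline, and Days 14 and 28 supply the on-treatment values.

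**The case against.** The strongest case against the point has four parts.

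- **Symptoms are captured.** Section 9.1.4 collects adverse events from the first dose to follow-up, by non-leading question and by spontaneous report. Section 10.4 summarises them for active and placebo. A reader might infer that an orthostatic effect would go undetected altogether. The documents do not support that: symptomatic dizziness can be reported and compared between arms. What is missing is the measured fall.
- **The screening reading has a use.** Section 6.3, criterion 1, excludes subjects with significant vital-sign abnormalities, so the standing reading can serve eligibility. A reader might infer that it serves no safety purpose, or that section 8.5.2 contradicts itself. Neither follows. The reading simply says nothing about the drug.
- **The early signal is thin.** It is two subjects, level with decreased appetite and limb pain, and it is not listed for the elderly cohort. Sections 7.2.4 and 11.3 name only headache among specific events. The most relevant experience is the first multiple-dose cohort, 50 mg once daily for 28 days. The protocol calls that dose safe and tolerable, but part of section 7.2.3 was not in the text available here, so any postural findings in it are unseen.
- **The link to blood pressure is indirect.** Section 3 expects improved blood pressure through better insulin sensitivity and related pathways, not through a postural mechanism.

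All four stand as limits on the strength of the claim. None puts a standing reading on the on-treatment schedule. A weak and uncertain signal is not a reason to leave out a short measurement in a placebo-controlled trial with safety in its primary objective.

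**Conclusion.** The point holds as a gap in measurement. The postural drop is available at 1 of 5 visits, at none on treatment, and never by arm. That conclusion rests only on the schedule in sections 7.3, 8.5 and 8.5.2 and Appendix B, and needs no assumption about the drug.

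How much the gap matters is less certain. It depends on two cases in 18 subjects (11.1%, 95% CI 1.4% to 34.7%) at pooled single doses without a stated comparator, on the admission of treated hypertensives, and on the place of safety in the primary objective. The documents do not establish that TRC150094 causes orthostatic hypotension, and this point does not claim that it does. It is a cheap improvement to the design. The trial's validity does not depend on it.

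**What to change.** In section 8.5.2, the visit lists in section 8.5 and Appendix B, extend the existing supine-then-2-minute-standing measurement to:
- Day 0, as baseline;
- Day 14;
- Day 28, before the catheters are placed, because section 8.4.1 keeps subjects supine for the clamp;
- Day 35, as an option.

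Split the vital-signs row of Appendix B into supine and standing. Record the time since the last dose at each on-treatment reading: section 7.2.3 puts the peak concentration within 3 h, so a reading without its dose time is hard to interpret. In section 10.4, add a descriptive summary by arm of the change in postural drop from Day 0, in line with that section's rule of no significance testing on safety data.

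The cost is about 2 to 3 minutes and a few extra data fields per visit, with staff and equipment already in use, plus the protocol and eCRF wording. If the sponsor prefers to keep the present schedule, section 8.5.2 should say why a reading at screening alone is enough.
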